## Methods

### Study Design

This study includes intervention development (Phase I), refinement (Phase II), and testing (Phase III). Such a design is appropriate when a number of research-related parameters (eg, adverse events, cost-effectiveness, feasibility, power calculation for sample size) remain unknown [25].

### Study Setting

This study is being conducted in the primary care setting and will be performed in the waiting room while parents and children await their upcoming pediatrician appointment. Specifically, we are working in partnership with colleagues who lead the Edmonton Oliver Primary Care Network (PCN), one of more than 40 PCNs in the province. In Alberta, PCNs were developed by our provincial health system to enhance and coordinate health services delivery in primary care. They include family physicians, a multidisciplinary team of health care professionals, decision makers, and administrators, all of whom work collaboratively to address the needs of the local patient population. This setting represents a suitable venue to address the primary and secondary prevention of childhood obesity because (1) PCNs are often families’ first point of contact with the health care system, (2) the goals and priorities of PCNs are aligned with primary and secondary prevention of chronic diseases, and (3) patients typically access health care services at PCNs throughout their lives, which represents an excellent setting to maintain contact with, and collect information from, families over an extended period [24,26].

### Phase I: Development

Our SBIRT tool, which we have titled the Resource Information Program for Parents on Lifestyle and Education (RIPPLE), will be developed in partnership with Evolution Health (EH), a Web-based intervention development company based in Toronto, Ontario [27]. Content in the SBIRT will be incorporated from current literature on children’s healthy lifestyle behaviors, including dietary, physical activity, and sedentary behavior habits, as seen in Slater et al [28] and a review by Steinbeck [29]. Theoretical underpinnings of the SBIRT will be informed by concepts used in existing interventions, for example, the Norm Activation Model [30]. Consistent with the Health Belief Model [31], the SBIRT will be designed to act as a *cue to action*, in which the intervention will prompt parents to initiate and sustain healthy lifestyle changes for their children. Specifically, the SBIRT will act as a trigger by creating a discrepancy between parents’ perceptions of their children’s dietary and physical activity habits and either *normative* or *injunctive* feedback—parents will receive either *normative* feedback on how their child relates to reference norms drawn from the Canadian pediatric population for eating [32] and physical activity [33], or *injunctive* feedback, which includes national recommendations [34]. By providing parents with two types of feedback, we will determine if injunctive or normative feedback is more salient for parents in the context of supporting their children’s healthy lifestyle behaviors.

Based on SBIRTs previously developed by Evolution Health [35,36], our SBIRT will *screen* children’s weight status, which will include sharing this information with parents, as well as deliver a *brief intervention* to parents related to their children’s lifestyle behaviors, and provide *referrals to treatment* and other supportive resources for parents. Specifically, the guided user interface (GUI) within the online program will include the following steps:

1. Data input. Children’s height (cm) and weight (kg) will be measured by the study-designated research assistant (RA) using a wall-mounted electronic stadiometer and an electronic medical scale. The RA will enter this data into the iPad program and then pass the iPad to the parent.

2. Screening. Parents will receive objective, personalized feedback both numerically, based on their children’s body mass index percentile, and visually, using a healthy weight ruler [37].

3. Brief theory-driven intervention. Parents will be randomly assigned to an intervention group, where they will complete one of four brief questionnaire-based interventions, or to the control group, *Heads Up!* The latter includes information on children’s lifestyle behaviors only. Two interventions will include nutrition-based questions—*Eat It!*—and two interventions will include physical activity-based questions—*Move It!* In each of the interventions, parents will receive either *normative* or *injunctive* feedback. Between-group differences in primary and secondary outcomes will be assessed to determine the differential impact of the intervention across the five groups of parents.

4. Toolkit. Parents will be presented with a menu of online resources and community services to choose from.

5. Theory-based measurement. To understand how the SBIRT works to influence parents’ intentions, a brief questionnaire has been adopted from Campbell et al [38] and will assess parents’ concern for, and motivation to, support children’s dietary and physical activity behaviors.

6. Tailored report. Parents will receive a personalized report that will include their children’s weight status, their responses to the intervention questions as well as the feedback they received, and the resources and services they selected from the toolkit*.*

To measure changes in primary (ie, parental concern for, and motivation to, support changes in children’s lifestyle behaviors) and secondary outcomes variables (ie, families’ use of resources and health services), parents will be contacted at 1-month follow-up to complete the same theory-based measurements they completed at baseline and a brief questionnaire to assess their use and/or intention to use the suggested resources and community services. By design, the SBIRT will require parents to indicate their preferred mode of contact for receiving the 1-month follow-up measure and questionnaire (eg, mail, telephone, email), which is designed to optimize participant retention.

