With these issues in mind, we hypothesize that an online SBIRT targeting parents will increase their awareness of their children’s weight status and enhance parents’ concern for, and motivation to, support their children’s healthy lifestyle behaviors. The program will have a prevention approach designed to benefit parents with children from across the body weight continuum. Specifically, our SBIRT will encourage parents of children with healthy weights to seek resources to eat healthfully and be physically active to maintain their children’s weight status. It will also guide parents of children with unhealthy weights to access information and health services to improve their children’s weight status and associated health risks. Our three-phase, multi-method study includes the following objectives:

1. Develop an online SBIRT tool designed to raise parents’ awareness of their children’s weight status and lifestyle behaviors.

2. Refine the SBIRT tool by assessing acceptability, satisfaction, and usability using focus groups with pediatric health care professionals, researchers, and parents.

3. Determine the feasibility (pilot-testing) and impact (pragmatic trial) of the intervention through a randomized controlled trial (RCT) design, which will include administering our SBIRT to a sample of parents and collecting data at baseline and 1-month postintervention to assess (1) changes in parents’ concern for, and motivation to, support children’s dietary and physical activity behaviors—primary outcome—and (2) families’ use of resources and health services for the prevention of childhood obesity—secondary outcome.

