Primary health care providers at this site have historically had around 2500 patient encounters per year [51], so our research staff will recruit families on approximately 2 days per week over several months to accumulate our study sample. Given the design of the SBIRT, parents will also need adequate time to complete everything at once (ie, saving and completing the intervention at a later date will not be possible within the SBIRT). With time constraints in mind, families will be approached to participate in the study if we—clinical/administrative staff, research team—believe parents will have sufficient time (ie, 15 to 20 minutes) to complete the intervention and research procedures while waiting for their scheduled clinical appointment. Although it is a potential barrier that some recruited parents may be unable to complete the program while they wait, previous studies have supported the feasibility of brief online interventions under similar conditions, for example, Freeborn et al [52]. Assuming 20 to 30% attrition at 1-month follow-up [53], complete data from approximately 150 parents is expected. Figure 1 represents a flow diagram of expected recruitment and retention. Based on primary care client demography, this sample size will allow us to enroll a diverse group of families that vary by age, ethnicity, family income, and weight status.

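### The concern and motivation score that serves as baseline is taken after the randomised intervention, so change to 1 month estimates the 1-month effect minus the immediate effect

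*Protocol article*

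**What the plan says.** In the Protocol article, Phase I: Development, "the guided user interface (GUI) within the online program will include the following steps". These are numbered 1 to 6:

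- Step 1: the research assistant enters the child's height and weight.
- Step 2: "2. Screening. Parents will receive objective, personalized feedback both numerically" and visually. This goes to all parents.
- Step 3: "3. Brief theory-driven intervention. Parents will be randomly assigned to an intervention group" or to the information-only control.
- Step 4: the toolkit menu of resources and services.
- Step 5: "5. Theory-based measurement. To understand how the SBIRT works to influence parents’ intentions, a brief questionnaire has been adopted". It covers concern and motivation, which is the primary outcome.
- Step 6: the tailored report.

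The text after the list says that "parents will be contacted at 1-month follow-up to complete the same theory-based measurements they completed at baseline". Objective 3 in the Introduction sets the primary outcome as "collecting data at baseline and 1-month postintervention to assess (1) changes in parents’ concern for, and motivation to" support the child's diet and activity. The Abstract also defines it as change. Data Collection refers back to Phase I for the questionnaire and names no earlier administration. Data Management and Analysis plans a hierarchical linear model of group changes, with baseline and 1 month as the time points.

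**The concern.** A baseline should be measured before the exposure whose effect is being estimated. Here the only described in-session score follows the randomised content, so it already contains any immediate effect of that content. An immediate effect is what the authors expect: Phase I describes the tool as a cue or trigger that works by showing parents a discrepancy. Subtracting a score that contains this effect removes it from the result.

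The primary outcome is at stake, and so is a later decision. Study Strengths says Phase III will supply preliminary effect sizes for the sample size of a cluster trial. Effect sizes based on change from Step 5 would be wrong for that purpose. The weight feedback and toolkit also reach every arm before Step 5, so change within an arm cannot show the effect of the whole tool either.

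**Working it through.** **The plan's own figures.** 5 arms × 40 = 200. With 20%, 25% and 30% attrition, 200 × 0.80 = 160, 200 × 0.75 = 150 and 200 × 0.70 = 140. This agrees with the stated figure of approximately 150, or 150 / 5 = 30 completers per arm. The document gives no effect size, SD or correlation for this outcome.

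**Algebra, free of assumed values.** Let D0 be the between-arm effect at Step 5 and D1 the effect at 1 month. Randomisation makes the expected difference before Step 3 equal to zero.

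- Change from a pre-Step 3 score: D1 − 0 = D1.
- Change from the Step 5 score: D1 − D0.
- 1-month score adjusted for Step 5, with equal SDs and within-arm correlation ρ: D1 − ρ × D0.
- 1-month score alone: D1.

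**Illustration.** Assumptions not in the document: D0 = 0.5 SD and ρ = 0.6. All effects are in SD units.

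| Share of D0 retained | True D1 | Change from pre-score | Change from Step 5 | Adjusted for Step 5 |
|---|---|---|---|---|
| 0% | 0.00 | 0.00 | −0.50 | −0.30 |
| 50% | 0.25 | 0.25 | −0.25 | −0.05 |
| 60% | 0.30 | 0.30 | −0.20 | 0.00 |
| 80% | 0.40 | 0.40 | −0.10 | 0.10 |
| 100% | 0.50 | 0.50 | 0.00 | 0.20 |
| 120% | 0.60 | 0.60 | 0.10 | 0.30 |

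A simulation with 200,000 parents per arm agrees. At 0%, 50% and 100% retained, change from Step 5 gave −0.495, −0.250 and −0.002; change from a true pre-score gave 0.004, 0.246 and 0.500; the 1-month score alone gave 0.002, 0.248 and 0.502.

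**Chance of a significant result.** Two-sided 0.05 is assumed (the article does not state sidedness), with 30 completers per arm and a normal approximation. The SD of a change score is √(2 × (1 − 0.6)) = 0.894.

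- Four arms pooled against control: SE = 0.894 × √(1/120 + 1/30) = 0.183. Full persistence measured from a true pre-score: 0.50 / 0.183 = 2.74, power about 78%. Measured from Step 5 the expected contrast is 0, so a significant positive result has probability 2.5%.
- One arm against control: SE = 0.894 × √(2/30) = 0.231. From a true pre-score: 0.50 / 0.231 = 2.17, power about 58%. From Step 5: again 2.5%. With ρ from 0.5 to 0.7, the 58% becomes 49% to 71%.
- 60% retained, change from Step 5: the expected contrast is −0.20. The chance of a significantly negative result is about 19% pooled (0.20 / 0.183 = 1.10) and about 14% for one arm against control (0.20 / 0.231 = 0.87).

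**The case against.** The strongest reply is that the step list may be incomplete. Demographic questions and the preferred mode of contact are collected within the tool but are not among the six steps, so a questionnaire before Step 3 could also have been left out. The case report form and Figure 1, which might settle this, are not shown. It is therefore right to say *as described*. But no text mentions an earlier administration, and the questionnaire, unlike the demographic items, does have a stated place in the sequence.

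A second reply is that the analysis is not confined to change. The article also plans between-group comparison at each time point, and randomisation protects both the Step 5 and the 1-month comparison. That is correct and limits the damage. It does not remove the problem, because the stated primary outcome is change and no analysis plan can recover a pre-intervention score that was never collected.

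A reader might infer four stronger things that the documents do not support:

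- *That every effect size from Phase III would be meaningless.* Only estimates based on change from Step 5, or adjusted for it, are affected.
- *That adjusting for Step 5 would show no effect when the effect persists.* In the illustration it shows 0.20 SD instead of 0.50. It reaches zero or below only when the retained share is at or below ρ.
- *That a fading benefit would be reported as harm.* The expected sign is wrong, but at 60% retained a significantly negative result occurs only about 19% of the time, so the usual report would be non-significant.
- *That more parents in the intervention arms would be called away before Step 5.* The tool cannot be paused ("saving and completing the intervention at a later date will not be possible within the SBIRT"), but nothing indicates that interruption differs by arm. Parents are approached only if they are thought to have enough time, and the pilot checks completion time.

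**Conclusion.** The point holds for the primary outcome as the article defines it. Change from Step 5 to 1 month estimates D1 − D0, which measures persistence after the session and not the effect of the intervention. This follows from the order of the steps and from randomisation, whatever the effect size or correlation. Only the size is illustrative: with D0 = 0.5 SD fully retained, ρ = 0.6 and 30 completers per arm, the chance of a significant positive finding falls from about 78% (pooled) or 58% (one arm against control) to 2.5%. The pooled contrast is itself an assumption, since the article compares five groups. The trial is not uninterpretable, because the 1-month scores compared directly between arms remain unbiased. The conclusion would change only if an unshown form placed the same questionnaire before Step 3.

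**What to change.** **Preferred.** Give the concern and motivation questionnaire after consent and before Step 2, or at the latest before Step 3. Define the primary analysis as the 1-month score by arm, adjusted for that pre-intervention score. The change is to the order of one brief questionnaire plus protocol and registry wording, and the article already allows changes to procedures after the pilot.

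The cost is a choice. If the questionnaire is moved, the immediate post-session measure is lost, and Step 5's stated purpose suggests the authors want it. If it is given twice, it adds some minutes to a session of 15 to 20 minutes. Answering first may prime parents, but equally in all arms. If the Step 5 score is kept, report it as a separate immediate outcome.

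**If the order cannot change.** Relabel Step 5 as immediate post-intervention. Define the primary outcome as the between-arm difference in the 1-month score, with no subtraction of Step 5 and no adjustment for it. Use that difference for any effect size carried into the cluster trial. This costs precision: under the assumptions above (D1 = 0.50), power for one arm against control is about 49% from the 1-month score alone, against about 68% with adjustment for a true pre-intervention score (SE = √(1 − 0.6²) × √(2/30) = 0.207; 0.50 / 0.207 = 2.42).

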### Phase II: Refinement

Following intervention development, focus groups with parents of children aged 5 to 17 years, along with pediatric-focused health care professionals (ie, primary, secondary, and/or tertiary providers with experience in childhood obesity prevention and management), health services administrators, and researchers (ie, faculty and trainees in the field of pediatrics and obesity) will be used to assess acceptability, satisfaction, and usability of the SBIRT tool. Parents will be recruited via word of mouth at the local university where the research is being conducted—a minimum of 10 parents will be recruited in order to gain an adequate representation of the caregiver perspective. Consistent with reports regarding the difficulties in organizing and running focus groups with specific populations [39,40], mechanisms to obtain parents’ perspectives (eg, one-on-one individual interviews) will be used if necessary. Using the recruitment technique of snowball sampling, health care providers, administrators, and researchers (n=20-25) will be purposefully sampled for demographic variation in participant groups (eg, disciplinary orientation, experience). This estimated sample size is consistent with methodological recommendations [41] and similar previous investigations [42,43], which will enable us to attain a high level of data saturation.

In a private room, the RA trained in facilitating focus group interviews will provide eligible participants with a study explanation and formal invitation to participate—informed, written consent will be obtained. Focus groups—6 to 8 participants per group—will occur over four to five sessions, and be 60 to 90 minutes in duration. The RA will lead groups step by step through the SBIRT (version 1.0) by entering standardized data into the GUI and projecting the Web-based content onto a screen. Interviews will include open-ended questions to query (1) participants’ overall impressions of the intervention, (2) factors related to participants’ acceptability of, and satisfaction with, the intervention, and (3) theoretical underpinnings of the SBIRT. Probes will include prompts on SBIRT perceptions, preferences, and how to best incorporate the program into existing clinical processes—perceived strengths, limitations, and areas for improvement will also be explored. A closing discussion will query perceptions of the need for long-term support within and beyond primary care and how this support should be provided.

Focus group discussions will be transcribed in real time using a court reporter, which optimizes transcription accuracy and ensures confidentiality [44]. Data will be managed and analyzed using NVivo 10 (QSR, Melbourne, Australia). Qualitative data analysis is a cognitive process that includes comprehending, synthesizing, theorizing, and recontextualizing [45], and the method of qualitative description [46] will be used to develop a basic description of the data. Data will be analyzed in a line-by-line process. From the initial analysis, a coding scheme will be developed to identify all meaningful units and new themes will be added as necessary. Once each discussion is coded, themes will be grouped under general categories and a written description will be constructed to explain each category. To enhance methodological rigor, we will (1) triangulate participants’ views by interviewing health care professionals, researchers, and parents, (2) employ concurrent data collection and analysis to inform amendments to the interview guide, and (3) implement a real-time member-checking protocol to ensure findings accurately reflect participants’ personal perspectives—at the end of each group, the moderator will confirm and clarify discussed themes [39].

### Phase III

#### Pilot-Testing

The objective of this phase is to pilot-test the refined SBIRT with parents (n≈30) to determine the feasibility of incorporating the intervention in primary care, including (1) accuracy of the randomization procedures, (2) ability to retain participants at follow-up, (3) practicality of clinician involvement, (4) suitability of the primary and secondary outcome measures, and (5) time to complete the intervention in the primary care waiting room. All of these elements are important to assess prior to determining the effectiveness of a newly developed intervention [25,47]. Upon recruitment and 1-month follow-up, the researchers will cease participant recruitment for a 2-week period to assess issues regarding feasibility—at this time, modifications may be made to study processes and procedures before initiating the pragmatic trial.

#### Pragmatic Trial

##### Trial Design

A parallel-group, double-blinded randomized controlled trial will be used to assess the effectiveness of the intervention. The trial has been registered publically (ClinicalTrials.gov identification number: NCT02330588) [48] and adheres to CONSORT guidelines [49]. Participants will be recruited and enrolled by an RA and RIPPLE will assign a unique, nonidentifying number to participants. The allocation sequence will be electronically generated within the GUI and to reduce the risk of selection bias, participants (n=200 parents) will be randomly assigned to one of five groups—*Eat It!* (normative), *Eat It!* (injunctive), *Move It!* (normative), *Move It!* (injunctive), or *Heads Up!* (control group). Group assignment will be done using blocked randomization—five arms, block size of five—to ensure equal group sizes—n=40/arm, equal allocation ratio of 1:1—throughout the study. To reduce the risk of performance bias, the RCT will be double-blinded. Specifically, the study-designated RA ([name]) will not be aware of participants’ intervention assignment, unless participants request assistance with the program, thus potentially revealing their assignment. Research personnel will be blinded for the remainder of the research process, including outcome assessment, in order to minimize the risk of detection bias [50]. As well, study participants will not be aware of their assignment to the intervention or control groups. Prior to the intervention, participants will receive information that is sufficient to obtain informed consent, but inadequate so as to decipher between intervention groups. Although contamination is a possibility given the close proximity of participants, given that only one participant can be recruited at a time, enrollment and recruitment will be staggered and the opportunity for participants to discuss the intervention with each other is unlikely.

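### A fixed, published block size equal to the number of arms lets any assignment the recruiting assistant happens to learn narrow the rest of that block; a small weakness that is cheap to remove

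*Protocol article*

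**What the plan says.** Under Trial Design, the protocol article says that "participants (n=200 parents) will be randomly assigned to one of five groups", with "equal allocation ratio of 1:1" (meaning equal shares across the five arms). The method is stated as: "Group assignment will be done using blocked randomization—five arms, block size of five—to ensure equal group sizes—n=40/arm". No variation of block size is mentioned.

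On concealment and blinding, the same section says: "The allocation sequence will be electronically generated within the GUI". It also says: "Participants will be recruited and enrolled by an RA". The RA "will not be aware of participants’ intervention assignment, unless participants request assistance with the program, thus potentially revealing their assignment". Parents are enrolled one at a time, and other research personnel stay blinded. The Abstract describes recruitment from one primary care pediatric clinic.

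Under Sampling and Recruitment, the clinic nurse identifies eligible families and the RA approaches them. The time condition is that "families will be approached to participate in the study if we—clinical/administrative staff, research team—believe parents will have sufficient time".

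Under Phase I: Development, the RA measures the child, enters the data and hands over the tablet. Screening feedback follows, and the parent is randomised only after that.

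**The concern.** Five arms in blocks of five is the smallest balanced block possible. Its size is constant and printed in the public protocol. The person who enrols every parent in sequence can count where a block begins and ends, and is also the person the protocol says may be unblinded. An assignment learned in one session therefore carries information about the parents who come next.

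The control-versus-active contrast is the most exposed. There is one control per block, so a single sight of it settles that everyone left in the block is active. The arms are also easy to tell apart once seen: nutrition questions, physical activity questions, or information only.

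At stake is the protocol's reliance on its allocation scheme to limit selection bias. Whether a family has enough time to be approached is a judgement, and an expectation about the next arm could influence it, even unintentionally. The primary outcome is parents' self-reported concern and motivation, so a difference between arms in the kind of family recruited could appear in the comparison.

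**Working it through.** **Inputs from the document (Trial Design):** 200 parents, five arms, fixed block of five, 40 per arm, one-at-a-time enrolment by an RA who may learn an arm when help is requested.

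**Assumed input:** q, the probability that the RA learns a given assignment. The document gives no rate, so a range is shown. Sightings are taken as independent, and the RA is taken to know the block size and its boundaries.

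**1. The plan's own figure.** 200/5 = 40 per arm, and 200/5 = 40 complete blocks. This reproduces.

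**2. Ceiling (q = 1).** With all earlier assignments in the block known, the chance of a correct guess at positions 1 to 5 is 1/5, 1/4, 1/3, 1/2 and 1.
- Sum = 2.283 per block; 2.283/5 = 45.7%, against 20% by chance.
- The fifth allocation is certain in every block: 40 of 200 (20%).
- Control versus any active arm: if the control falls at position k, the 5 − k later allocations are certainly active. If it falls fifth, that one is certain too. Mean = (4+3+2+1+0)/5 + 1/5 = 2.2 of 5 (44%).

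**3. Partial knowledge (q < 1).** At position k, the number m of earlier assignments seen is binomial(k − 1, q), and the guess is right with probability 1/(5 − m). The guess rate is the mean of E[1/(5 − m)] over k = 1 to 5.
- q = 0.10: (0.2000 + 0.2050 + 0.2103 + 0.2161 + 0.2222)/5 = 0.211
- q = 0.25: (0.2000 + 0.2125 + 0.2271 + 0.2445 + 0.2664)/5 = 0.230
- q = 0.50: (0.2000 + 0.2250 + 0.2583 + 0.3063 + 0.3875)/5 = 0.275

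Simulation agrees to within 0.1 percentage point.

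The chance that the control has already been seen in the block is q(k − 1)/5 at position k, which averages 0.4q. The fifth allocation is certain with probability q⁴, so 40q⁴ blocks are expected to have a certain fifth.

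| q (assumed) | Correct guess | Control already seen | Blocks of 40 with a certain fifth |
|---|---|---|---|
| 0.10 | about 21% | 4% | 0.004 |
| 0.25 | about 23% | 10% | 0.16 |
| 0.50 | about 28% | 20% | 2.5 |
| 1 | 45.7% | 40% | 40 |

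**4. Randomly varied blocks, worst case.** These figures come from 600 simulated trials of 200. The guesser knows every earlier assignment and the set of possible sizes, and updates the probabilities exactly.

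| Block sizes | Certain | Correct guess |
|---|---|---|
| 5 only | 20.0% | 45.7% |
| 5, 10 | 6.5% | 42.1% |
| 5, 10, 15 | 3.2% | 39.8% |
| 10, 15 | 4.0% | 38.8% |

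**The case against.** A reader might infer that the recruiting assistant can see the assignments, so that the last place in every block is known in advance. The document does not support that. The RA is unaware of the arm by default, and the exception is limited: "unless participants request assistance with the program, thus potentially revealing their assignment". The fifth allocation is certain only if all four before it were revealed. At q = 0.25 that is expected in 0.16 of 40 blocks.

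The safeguards are real. The tool allocates after enrolment, once the tablet is with the parent, so there is no list or envelope to consult. The nurse identifies eligible families. Approach is judged jointly by clinic and research staff on available time, and nothing in the document suggests that it is steered by expected arm. For siblings, a birthday rule removes the choice of child.

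Nor should block size be blamed for the unblinding itself. That comes from help requests and would persist under any scheme. Block size governs only what a revealed arm says about later parents, and parents complete the outcome questionnaires themselves. The trial also seeks preliminary effect sizes for a later cluster trial, which limits the stakes.

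All of this stands, and it makes the point minor. It does not remove it: in-tool generation prevents reading the sequence ahead, but not inference from a revealed arm plus a known block size. The document neither states nor bounds how often arms are revealed.

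**Conclusion.** The point holds as a minor design weakness. The fixed block of five for five arms, combined with a channel that the protocol itself acknowledges to the person who enrols, makes later allocations somewhat more predictable than they need be.

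On assumed reveal rates of 10% to 50%, correct guessing rises by about 1 to 8 percentage points above the 20% expected by chance. The figures of 45.7% guessed and 40 of 200 certain are ceilings that require every earlier assignment to be known, and should not be quoted as the expected leak.

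The result rests on independent sightings and on the RA knowing the block size and boundaries. It shows opportunity for selection bias, not evidence that any would occur.

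**What to change.** Before the pragmatic trial, program the tool to draw block sizes at random in multiples of five, for example 5, 10 and 15. Keep the sizes from the RA and clinic staff, and state in the public text only that they vary. Have the RA log each session in which the arm was seen, so that the reveal rate can be reported. The pilot of about 30 parents already examines the randomisation procedures and allows changes afterwards, so it could supply a first count of help requests.

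The gain is mainly in certainty: in the worst case certain allocations fall from 20% to about 3%, while correct guessing falls only from 45.7% to about 40%. Non-disclosure and the log are therefore essential parts of the change.

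The cost is one change to the randomisation code and a short log. Random sizes need not end a block at 200, so arms may differ by up to about 3 parents, unless the final block is constrained to end there and keep 40 per arm.
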